# Evaluation of treatment response, drug resistance and HIV-1 variability among adolescents on first- and second-line antiretroviral therapy: a study protocol for a prospective observational study in the centre region of Cameroon (EDCTP READY-study)

**DOI:** 10.1186/s12887-019-1599-z

**Published:** 2019-07-05

**Keywords:** HIV, Antiretroviral therapy, Adolescents, Cameroon

## Abstract

**Background:**

Sub-Saharan Africa (SSA) alone has nine out of every 10 children living with HIV globally and monitoring in this setting remains suboptimal, even as these children grow older. With scalability of antiretroviral therapy (ART), several HIV-infected children are growing towards adolescence (over 2.1 million), with the potentials to reach adulthood. However, despite an overall reduction in HIV-related mortality, there are increasing deaths among adolescents living with HIV (ADLHIV), with limited evidence for improved policy-making. Of note, strategies for adolescent transition from pediatrics to adult-healthcare are critical to ensure successful treatment response and longer life expectancy. Interestingly, with uptakes in prevention of mother-to-child transmission, challenges in ART programs, and high viremia among children in SSA, the success rate of paediatric ART might be quickly jeopardised, with possible HIV-1 drug-resistance (HIVDR) emergence, especially after years of paediatric ART exposure. Therefore, monitoring ART response in adolescents and evaluating HIVDR patterns might limit disease progression and guide on subsequent ART options for SSA ADLHIV.

**Objectives:**

Among Cameroonian ADLHIV receiving ART, we shall evaluate the rate of immunovirologic failure, acquired HIVDR-associated mutations, HIV-1 subtype distribution, genetic variability in circulating (plasma) versus archived (cellular) viral strains, and HIVDR early warning indicators (EWIs) at different time-points.

**Methods:**

A prospective and observational study will be conducted among 250 ADLHIV (10–19 years old) receiving ART in the centre region of Cameroon, and followed-up at 6 and 12 months after enrollment. Following consecutive sampling at enrolment, plasma viral load and CD4/CD8 count will be measured, and genotypic resistance testing (GRT) will be performed both in plasma and in buffy coat for participants experiencing virological failure (two consecutive viremia > = 1000 copies/ml). Plasma viral load and CD4/CD8 will be monitored for all participants at 6 and 12 months after enrolment. HIVDR-EWIs will be monitored and survival analysis performed during the 12 months follow-up. Primary outcomes are rates of virological failure, acquired-HIVDR, and mortality.

**Discussion:**

Our findings will provide evidence-based recommendations to ensure successful transition from paediatrics to adult ART regimens and highlight further needs of active ART combinations, for reduced morbidity and mortality in populations of ADLHIV within SSA.

**Electronic supplementary material:**

The online version of this article (10.1186/s12887-019-1599-z) contains supplementary material, which is available to authorized users.

## Background

Sub-Saharan Africa (SSA) alone carries 69.9% of the 36.9 million people infected worldwide and 65.8% of the 1.2 million the global AIDS-related deaths by end 2014, the majority occurring among adolescents [1]. With the highest burden of paediatric HIV infections (2.3 million), about nine out of every 10 children living with HIV found in the SSA region. With about 86.4% of the 220,000 newly infected children worldwide by end 2014 [1], the number of children living with HIV/AIDS will continuously increase overtime, thereby predicting a growing rate of adolescents living with HIV (ADLHIV) in this region. In this line, the burden of HIV/AIDS constitutes a continuous major threat for the future development of SSA countries, and therefore remains a leading poverty-related disease in the entire continent [1–3].

With the advent and scalability of Antiretroviral therapy (ART), there is a global decrease in AIDS-related deaths. Of note, 15.8 million people living with HIV were accessing ART as of June 2015, of which 67.7% were from SSA. Interestingly, about 94% of all children receiving ART are from SSA, a number expected to reach 1.5 million children by 2020 [1, 2]. In this context of continuous new HIV paediatric infections and increasing coverage in paediatric ART, the number of children living with HIV will increase, suggesting a higher likelihood of reaching adolescent age and even adulthood if treatment regimens remain fully effective in controlling HIV infection [2–4]. Most importantly, out of about three million children are living with HIV, an estimated 2.1 million were ADLHIV (10–19 years of age) in resource-limited settings (RLS) by end 2012, with a consistent rising of HIV-related deaths in these ADLHIV even though regressions are seen in other target populations (younger children, pregnant women, adults living with HIV/AIDS) [5]. ADLHIV therefore constitutes an HIV population with growing health concerns and with very limited findings for generalisable best practices specific to this target population, especially in SSA whereby, compared to the western world, there is persistent suboptimal monitoring strategies in routine practice [6–8].

With the increasing scale-up of ART, as high as 20% of children might experience virological failure (VF) in RLS, in the frame of high-levels of viremia generally observed in children. Moreover, as these children grow older, there are increasing risks of treatment failure associated to the development of HIV drug resistance (HIVDR), particularly with the limited therapeutic options available for clinical management [7, 8]. Current paediatric first-line regimens consist of lamivudine, plus abacavir or zidovudine, plus ritonavir-boosted lopinavir (LPV/r) or nevirapine (NVP), depending on the mother-child pair’s history of prevention of mother-to-child transmission (PMTCT) [6]. of note, LPV/r overcomes non-nucleoside reverse transcriptase inhibitor (NNRTI) resistance resulting from PMTCT exposure [2, 3, 9], while NVP matches with current postnatal prophylaxis [3, 8, 9]. The success of this lifelong paediatric treatment will largely depends on the effectiveness of the combination ART from childhood and monitoring overtime [8–14]. Current uptakes in PMTCT interventions and universal ART for children suggest that any infected child stands at high risk of transmitted or acquired HIVDR. Such risks are likely higher in a context whereby: (1) PMTCT practices have been varying overtime (from single dose nevirapine, AZT, to options B and B+), (2) commonly available antiretrovirals are drugs with low genetic-barrier to resistance, (3) drug stock-outs are frequently reported and (4) poor adherence remains challenging. Furthermore, these factors are associated with clinical challenges of which the high viremia in children and the limited laboratory monitoring offer room for delayed detection of treatment failure with accumulation of HIVDR mutations at rates as high as 80% [8, 10, 11, 15–21]. This situation limits therapeutic option as children grow older in SSA, thereby appealing for effective public health strategies for optimal sequencing of ART regimens, in order to maximise long-term treatment success and reduce AIDS-related morbidity and mortality in these RLS [8]. Most importantly, as older children require transitioning from pediatrics to adult ART regimens, sustaining long-term viral suppression prompts the need for reduced risks for mortality among ADLHIV in SSA [5]. With scarcity of evidence that reduces disease progression while preserving next therapeutic options for this growing population of individuals in SSA, there is need to implement an assessment that would guide efficient public health strategies in ART program performance for adolescents [2, 8].

As VF is generally associated with emerging HIVDR, assessing drug resistance mutations (DRMs), in the context of a failing regimen, provides clinical benefit and reduced mortality [9, 10, 22]. An evidence guiding selection of first- and second-line pediatric ART regimens, revealed an urgent need for alternative pediatric treatment options in RLS [23]. Furthermore, Kityo et al. in Uganda revealed high prevalence of pre-treatment HIVDR and a decreasing burden as children grew older (10% of all children versus 15.2% of children < 3 years),implying that adolescents might have archived resistant strains after years of chronic infection [24]. Similar findings from East-Southern Africa reported high-levels of pediatric HIVDR, ranging from 29 to 77% based on PMTCT history, and decreasing rates of DRMs with increasing ages, thus confirming the fading-up of resistant strains over the fitness of wild-type species [11].

As aforementioned, DRMs fade-up as children grow older, and might remain occult in minority viral populations or in the cellular reservoirs [25]. For adolescents vertically infected with HIV, the mechanism of occult HIVDR might be driven by archiving in cellular reservoirs, due to the long-term chronic infection. Of note, our studies among children (aged 1–12 years) with wild type viruses revealed minority DRMs only at early age (1 year), supporting the fact that ADLHIV stand at higher chances of harbouring archived DRMs [26]. Of note, theseoccult resistant variants might remain hidden, ready to repopulate plasma from tissues/reservoirs under pharmacological pressure [11]. The potential presence and the eventual relevance of these minority variants in paediatric settings can be substantial, and merit attention in the frame of limited therapeutic regimens. Demonstrating the clinical implications of such archived DRMs remains an important unmet medical need [26]. In this light, assessing such archived DRMs among adolescents might provide complementary information with an added value for the sequencing of fully active ART combinations, and in turns increase their life expectancy.

When evaluating the efficacy of first- and second-line pediatric ART regimens in RLS, Boerma et al. reported the necessity to set-up salvage pediatric therapies that could be affordable options in RLS [23]. This entails an eventual need of newer second-line or third-line ART regimens. In this line, we earlier demonstrated the absence of major DRMs in the integrase region among ART-naïve, first- and second-line treated patients (including adolescents) in Cameroon, thus indicating a potential efficacy of integrase inhibitors (raltegravir, elvitegravir or dolutegravir) even in heavily treated patients [27, 28]. Furthermore, we also studied CXCR4 and CCR5 viral tropism to determine possible use of anti-CCR5. Our data revealed high rates of X4-tropic viruses among Cameroonian patients, thereby suggesting poor outcomes of CCR5 antagonists (i.e. maraviroc) if used for a public health approach (i.e. without tropism testing) [27–30]. Most importantly, our data from next generation sequencing revealed R5-variants prevailing among children under five years old [26], with increasing proportions of X4-variants, in accordance with previous reports [29, 30]. Thus, pending prospective investigations, a potential salvage ART regimen for adolescents failing ART might contained fully active reverse transcriptase inhibitors (RTIs) and/or protease inhibitors in combination with integrase inhibitor (raltegravir), as an affordable public health approach in RLS [14, 27, 28].

Within the SSA-settings, few studies have addressed the needs of ADLHIV. In South-Africa, a study comparing treatment outcomes between adolescents versus young adults at a public sector community-based ART revealed lower virological suppression rates and higher rates of VF among adolescents [31], thus underscoring the necessity for closer monitoring strategies and the eventual needs of subsequent salvage therapies [23]. In the Central African Republic, an assessment of virologic response and DRMs revealed 34% of children in need of a second-line ART after first-line failure, while 47% of those under second−/third-line ART were experiencing VF with at least one major DRM to RTIs, thus calling for urgent need for improved pediatric ART and monitoring strategies. Among Cameroonian children (aged up to 12 years), we earlier reported high rates (~ 90%) at first-line failure, after a median-time-on-ART of about two years only. Second-line guided by sequencing data showed ~ 70% with virological suppression and ~ 90% with viremia less than 1000 copies/ml. HIV-1 diversity did not interfere with emerging DRMs and CD4 showed a poor sensitivity is predicting treatment response [18]. However, data on medium- to long-term follow-up are completely missing, and recent findings showed potential implications of genetic diversity on virological response, especially among CRF02_AG infected populations [32–35], with considerable programmatic challenges as in Cameroon [36, 37]. While attempting to ascertain AIDS events among adolescents, Sharp et al. reported that, among vertically infected adolescents, the region of HIV-1-Gag targeted by CD8+ T cells as well as the magnitude of CD8+ response may have a clinical importance on monitoring disease progression [38]. With limited evidence in the management of ADLHIV in SSA, it would therefore be of great asset to thoroughly evaluate the immunovirologic response in this target population, in order to identify individual and programmatic factors to be tackled for improved quality of life and life expectancy among ADLHIV. Such analysis will help in tailoring treatment response, resistance profiling and adequacy to subsequent (second- or third-line) ART regimens for ADLHIV in need of newer therapeutic options in SSA.

The READY-Study (*Resistance Evolution among Adolescents in Yaoundé and its surroundings*) aimed at generating information towards improved recommendations for a successful long-term management of ADLHIV in SSA, with adequate and affordable transition policies from paediatric to adult ART regimens in these RLS. Among Cameroonian adolescents (10–19 years old) receiving ART, we shall monitor the therapeutic response to first- and second-line regimens, drug resistance profiling and HIV-1 genetic variability during one-year follow-up. In this population of adolescents receiving ART in Cameroon, we shall: (1) Evaluate the rate of immunovirologic failure in the entire population at enrolment, month-6 and month-12 follow-up points; (2) Evaluate acquired DRMs and HIV-1 subtype distribution among those experiencing VF at enrolment, month-6 and month-12 follow-up points; (3) Evaluate the genetic variability in circulating (plasma) versus archived (cellular) viral strains among those experiencing VF at enrolment, month-6 and month-12 follow-up points; (4) Evaluate HIVDR early warning indicators (EWIs), including survival analysis, in the entire study population through out the one-year monitoring period.

## Methods/design

### Study design

A prospective and observational study will be conducted among ADLHIV receiving ART as per the national ART programme in Cameroon, with follow-up at 6 and 12 months after enrollment.

ADLHIV on ART will be enrolled from four health facilities in the centre region of Cameroon, consisting of:Two health facilities from the referral treatment centres (the Mother-Child Centre of the Chantal BIYA foundation and the National Social Welfare hospital, both in Yaoundé);Two health facilities from the management units (the Mbalmayo District Hospital in Mbalmayo and the Mfou District hospital in Mfou).

After enrolment (month-0), follow-up will be done at mid-point (month-6) and at end-point (month-12), assessing immunological and virological response, including HIV-1 genotypic resistance testing (GRT) in case of confirmed treatment failure.

### Description of study setting

In Cameroon, a country with a generalised HIV epidemiology (4.3% prevalence in the general population) and a broadly diverse HIV strains (with the prevailing CRF02_AG recombinant) [32–36, 39], the centre region is among sites with high HIV burden (6.1%), and the locality of Yaoundé and its surrounding have a prevalence of 6.3% [40]. HIV prevalence among vertically infected children is still consistent (prevalence of 11.5%) in the country [40], and 1.2% of those aged 15–19 years are infected [39]. Altogether, these suggest a growing rate of ADLHIV in the country, with the centre region being among the most worrying. First-line ART regimens are widely used (96.3%, consisting of two nucleoside RTIs [NRTIs] plus one non-NRTI [NNRTI]) and second-line ART regimens (3.7%, consisting of one protease inhibitor and two NRTIs) are also available nationwide, with a total of 122,638 people receiving ART by end 2013 [41]. The most used regimens for adult are zidovudine plus lamivudine plus nevirapine, followed by tenofovir plus lamivudine plus efavirenz, while for children zidovudine plus lamivudine plus nevirapine and zidovudine plus lamivudine plus efavirenz are predominant [41]. In terms of ART coverage by age range, 4% of treated patients are aged 0–14 years versus 91% aged 15 and above (i.e. 5% unknown age), and adolescents (i.e. aged 10–19 years) are distributed between these two groups [41]. Importantly, the highest coverage of ART is in the centre region (Yaoundé and its surrounding), followed by the Littoral and the North-west regions [41]. The national strategic plan targets 80% ART coverage of children age 0–14 years by end 2015 [42], thus indicating a growing number of adolescents on ART.

The choice of the Centre region for the present study in Cameroon is therefore based on its high HIV burden, its high coverage of ART, the long-term experience in ART provision of health facilities [42], as well as the wide HIV-1 genetic diversity reported from vertically infected children and adolescents living in this geographical setting [18].

### Sampling method

A consecutive and non-randomised sampling method will be used for participant enrolment, according to eligibility criteria.

#### Eligibility criteria

##### Inclusion criteria

Will be enrolled in the study ADLHIV (aged 10–19 years), who are receiving a first- or second-line ART for ≥6 months in one of our study sites, who provide their written assent, whose legal guardian accept to provide a written informed consent (in addition to written assent provided by the adolescent), and irrespective of PMTCT antiretroviral history (exposed to PMTCT drugs, not-exposed to PMTCT drugs, or unknown exposure).

##### Non-inclusion criteria

Will not be considered for enrolment ADLHIV not found (i.e. not formally registered) in the ART monitoring system of a study site, ADLHIV reported to be ART-naïve, to be on a drug regimen not included in the national guidelines, or to be on a structured treatment interruption.

##### Exclusion criteria

Will be considered excluded from the study any participant who decides deliberately/freely to withdraw in the course of the study, or transferred out of a study site before mid- or end-point.

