#### Sample size

Assuming the rate of VF at 40%, a 95% confidence and 80% statistical power, sample size is 174 patients. Adding 10% potential LTFU during the one-year study period and 20% sequencing failure rate [10, 18], minimal sample size is 243 ADLHIV, rounded-up to 250 total sample size, further stratified into 150 ADLHIV in the referral centres (75 per site) and 100 in the HIV management units settings (50 per site), as per coverage in ART in these two geographical locations [41, 42].

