
**Table Taba:** 

EWI and title	Definition	Numerator	Denominator	Target
EWI_1_ On-time pill pick-up	Proportion of adolescents that pick-up ART no more than two days late at the first pick-up after the baseline pick-up.	Number of adolescents picking-up their ART “on time” at the first drug pick-up after baseline pick-up date	Number of adolescents who picked-up ARV drugs on or after the designated EWI sample start date	Desirable performance (green): > 90%Fair performance (amber): 80–90%Poor performance (red): < 80%
EWI_2_ Retention in care	Percentage of adolescents known to be alive and on ART 12 months after enrolment	Number of adolescents who are still alive and on ART 12 months after enrolment	Total number of adolescents (excluding transfers out) who were expected to achieve 12-month outcomes	Desirable performance (green): > 85%Fair performance (amber): 75–85%Poor performance (red): < 75%
EWI_3_ Pharmacy stock-outs	Percentage of months in the study period in which there were no ARV drug stock-outs	Number of months in the designated year in which there were no stock-out, days of any ARV drug routinely used at the site	12 months of the reporting period	Desirable performance (green): 100%Poor performance (red): < 100%;
EWI_4_ Pharmacy dispensing practice	Percentage of adolescents being dispensed a mono- or dual-ART	Number of adolescents who pick up from the pharmacy, a regimen consisting of one or two ARVs;	Number of adolescents picking up ART on or after the designated EWI sample start date	Desirable performance (green) defined as 0% adolescents picking-up a mono- or dual-ARTPoor performance (red) defined as > 0% adolescents picking-up a mono- or dual-ART, and
EWI_5_ Virological suppression	Percentage of adolescents receiving ART of ART whose viral load is < 1000 copies/ml 12 months after enrolment	Number of adolescents receiving ART 12 months after study enrolment and whose viral load is < 1000 copies/ml	Number of adolescents who have a viral load performed at 12 months after enrolment	Desirable performance (green): > 85% Fair performance (amber): 70–85%Poor performance (red): < 70%

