### Abstraction of HIVDR EWIs

Data on HIVDR EWIs will also be collected at each study phase, consisting of five variables among which EWI_1_ (*on-time pill pick-up*), EWI_2_ (*retention in care*), EWI_3_ (*pharmacy stock-outs*), EWI_4_ (*dispensing practices*), EWI_5_ (*virological suppression*). Among patients not retained in care during the 12-month follow-up period, we shall investigate to the underpinning reason that might be deliberate ART interruption, transfer out or mortality. Cases of mortality will then serve to determine the survival rate among the study participants.

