
At enrolment, midpoint and endpoint, prevalence of VF and HIVDR (with 95% Confidence Intervals) will be described globally, by geographical settings and by site. Associated factors will be evaluated using multivariate logistic regression, with an estimative approach for the unbiased effect of ART regimens (first versus second-line) and HIV-1 diversity (CRF02_AG versus non-CRF02-AG) [18]. In order to provide the highest level of evidence amongst ADLHIV experiencing VF versus those on virological success, ART response will be described through time to event data analysis and mixed models for the trajectory of CD4 count and viral load, based on adjustments of baseline confounders (duration of treatment, age, gender, orphan hood, site). The effect of DRMs (from plasma versus buffy coat) on ART response will be evaluated using multivariate survival models, either Cox or Fine&Gray in the presence of death as competing event. Characteristics of patients LTFU will be described and, if necessary, inverse probability weights will be used. Primary outcome is the proportion of VF; secondary outcome is the proportion of acquired-HIVDR, or deaths, evaluated according to study site (referral centres versus management units), HIV-1 subtype distribution (CRF02_AG versus non-CRF02-AG) [18], adherence levels (< 95% vs. ≥95%) [44], and ART regimens (first versus second-line) [35]. Proportion of adolescents with low-level viremia (≥400 or ≥ 50copies/ml) who finally end in VF will be described, along with HIVDR profile at endpoint [45]. We will build a multivariate logistic model with predictive approach to evaluate the association of socioeconomic conditions with adherence levels and HIVDR emergence [44, 46].

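### Withdrawal and transfer-out after enrolment are written as exclusion criteria, so the analysis population depends on later follow-up and these leavers fall outside the planned attrition handling

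*Protocol article*

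**What the plan says.** Under Eligibility criteria, the protocol article lists inclusion, non-inclusion and exclusion criteria separately. The non-inclusion criteria cover who may not enter. The exclusion criteria concern people already in the study: "Will be considered excluded from the study any participant who decides deliberately/freely to withdraw in the course of the study, or transferred out". The rule is tied to exits that happen ahead of the month-6 or month-12 visit. The section does not say whether data gathered before exit are kept, censored or dropped.

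Four other places bear on this:

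- **Aims (end of Background).** Immunovirologic failure is to be assessed in the entire population at enrolment, month 6 and month 12. The early warning indicators, including survival, cover the entire study population.
- **Data collection and analysis.** VF and resistance prevalence are reported at all three time points, and time-to-event and mixed models are planned. On attrition: "Characteristics of patients LTFU will be described and, if necessary, inverse probability weights will be used".
- **Early warning indicator table, EWI_2 (retention in care).** The denominator is "Total number of adolescents (excluding transfers out) who were expected to achieve 12-month outcomes". The numerator is those alive and on ART at 12 months.
- **Abstraction of HIVDR EWIs.** For patients not retained, "we shall investigate to the underpinning reason that might be deliberate ART interruption, transfer out or mortality".

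The Sample size section also allows for attrition, but only under the name of loss to follow-up: "Adding 10% potential LTFU during the one-year study period and 20% sequencing failure rate".

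**The concern.** An exclusion criterion that is met only by later events makes membership of the study population depend on follow-up. Read literally, an adolescent with a valid enrolment viral load who withdraws at month 4 is no longer part of the study, even for the enrolment prevalence of VF. Someone who transfers after month 6 would also drop out of the month-6 estimate.

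At month 12 these leavers have no viral load whichever way the rule is read. What exclusion removes there is the means of correction. Inverse probability weights need the leavers' baseline records, and the attrition sentence names only patients lost to follow-up.

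The primary outcome is the proportion with VF. If adolescents who leave are more often viraemic, those who remain look better than the enrolled population. For survival, the discarded follow-up is free of deaths by construction, because these participants were alive when they left. Dropping it instead of censoring it would raise the crude death rate.

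**Working it through.** **1. The plan's own figures.** The section starts from "Assuming the rate of VF at 40%, a 95% confidence and 80% statistical power, sample size is 174 patients", and then "minimal sample size is 243 ADLHIV, rounded-up to 250 total sample size". Inflating by N/(1 − d) in sequence:

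- 174/0.90 = 193.3, rounded up to 194
- 194/0.80 = 242.5, rounded up to 243

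The 243 reproduces. The sample size is not in dispute here. It supplies the assumed VF rate (40%) and the only attrition figure in the article (10%). The article does not say whether that 10% includes withdrawals and transfers.

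**2. Effect on VF prevalence.** Let p be VF among all enrolled, d the share excluded and v the VF rate among those excluded. The remaining cohort shows (p − d·v)/(1 − d). Here p = 40% comes from the Sample size section; d and v are assumptions, with d = 10% borrowed from the loss-to-follow-up allowance.

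| d | v | Observed VF | Shift (points) |
|---|---|---|---|
| 10% | 40% (non-informative) | (0.40 − 0.04)/0.90 = 40.0% | 0 |
| 10% | 60% | (0.40 − 0.06)/0.90 = 37.8% | −2.2 |
| 10% | 70% | (0.40 − 0.07)/0.90 = 36.7% | −3.3 |
| 5% | 60% | (0.40 − 0.03)/0.95 = 38.9% | −1.1 |
| 10% | 100% (extreme) | (0.40 − 0.10)/0.90 = 33.3% | −6.7 |

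For scale, the 95% half-width at n = 250 is 1.96 × √(0.40 × 0.60/250) = 6.1 points.

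**3. Effect on EWI_2.** The classes are "Desirable performance (green): > 85%Fair performance (amber): 75–85%Poor performance (red): < 75"%.

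- *Transfers.* The indicator's denominator already leaves them out, so excluding them from the study changes nothing.
- *Withdrawals.* The denominator does not remove them; the exclusion rule would. Assume 250 enrolled, 12 transfers, 12 withdrawals and 25 other losses. Then 250 − 49 = 201 are retained without counting any withdrawal, and the defined denominator is 250 − 12 = 238.
  - Withdrawals kept, none on ART at 12 months: 201/238 = 84.5% (amber)
  - Withdrawals kept, all 12 on ART: 213/238 = 89.5% (green)
  - Withdrawals dropped: 201/226 = 88.9% (green)

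The correct value therefore depends on the withdrawn adolescents' ART status, which dropping them ignores. The example is chosen to sit near the threshold: it has 49/250 = 19.6% leaving. If total loss were 10%, with no transfers and none of those lost counted as retained, retention would be 225/250 = 90%. That is already green, and dropping withdrawals could not change the class.

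**4. The passages side by side.** The aims refer to the entire population; the exclusion rule removes part of it. The attrition sentence covers loss to follow-up; the exclusion rule places withdrawals and transfers in a different category. No sentence in the article bridges either gap.

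**The case against.** The strongest reply is that the rule is only a discontinuation rule with an unfortunate label. Entry is already governed by the non-inclusion criteria, forms are sent to data entry after each visit, and the aims refer to the entire population. On that reading data to exit are kept, enrolment VF is untouched and survival can be censored at exit. The article is also condensed, and censoring dates and analysis sets commonly sit in a fuller document.

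Much of this stands. A reader might infer that the plan deletes earlier data; the text does not say so. But the benign reading is not written either, and the stated rule is that these participants are excluded from the study. The point is about that wording and does not rest on missing detail. Even on the benign reading, withdrawals and transfers remain unnamed in the attrition handling. Mixed and time-to-event models can use partial follow-up, but only if the records are retained.

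Three further inferences are not supported:

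- **A large established bias.** With 20% leaving and 70% of them failing, the shift would be 7.5 points ((0.40 − 0.14)/0.80 = 32.5%), more than the confidence half-width. Nothing in the article supports 20%, or any particular VF rate among leavers.
- **A contradiction over transfers.** It is tempting to see the investigation of reasons for non-retention as clashing with the EWI_2 denominator. The two can coexist: the investigation is a way of identifying the transfers that the denominator then leaves out.
- **Withdrawal as non-retention.** EWI_2 counts being alive and on ART. An adolescent may leave the research and stay in care, so scoring every withdrawal as not retained would bias the indicator downwards.

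**Conclusion.** The point holds as a badly fixed rule on who is analysed. Applied as written, it conditions the VF, resistance and survival results on not withdrawing or transferring, disagrees with the stated aims, and leaves these participants outside the planned attrition handling. Whether this biases VF depends on two quantities the article does not give. At 10% leaving with 60-70% of them failing, VF is understated by 2.2 to 3.3 points, about a third to a half of the confidence half-width. If exit is unrelated to VF, the bias is zero. For EWI_2 the issue is confined to withdrawals, and a change of performance class is possible under some assumptions but not shown. The rule bears on the primary outcome and is nearly free to correct, so it should be settled before analysis.

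**What to change.** - Rename withdrawal and transfer-out as discontinuations and remove them from the exclusion criteria.
- Keep every enrolled participant in the enrolment analyses and use all data up to exit, unless consent to data use is revoked.
- Censor at the date of exit in the time-to-event analyses.
- Extend the description of leavers and the inverse probability weights in Data collection and analysis to withdrawals and transfers, alongside loss to follow-up.
- For EWI_2, keep study withdrawals in the denominator and classify them by whether they are known to be alive and on ART at 12 months, not by having left the research. Transfers stay out of the denominator, as the table already states.

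The cost is a wording change and slightly more analysis work. The data up to exit are already being collected. The one added task is establishing 12-month ART status for withdrawn participants where their consent allows it.
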